### Data Collection Methods

Baseline and subsequent follow-up rounds will be conducted via structured, interviewer-administered surveys using REDCap tablet-based electronic questionnaires. These instruments have been developed by adapting core modules from the WHO STEPS [30] and the standardized DHS tools of the INDEPTH Network [20], ensuring alignment with established population-based surveillance practice. Household-level forms are linked to each HHID and capture location geocoordinates (imported directly from the mapping module), asset ownership, housing conditions, water and sanitation status, and records of vital events (births, deaths, and in- and out-migrations) since the last round. Individual-level forms are linked via a unique individual identification (INDID) nested within each HHID and address core sociodemographic factors (age, sex, marital status, education level, and occupation), women’s empowerment, and exposure to gender-based violence. Health-related modules capture self-reported history of NCDs (hypertension, diabetes, and cardiovascular disease), mental health status, and key communicable diseases (HIV, tuberculosis, and malaria), as well as reproductive health metrics. For each reported condition, data are also collected on prior diagnosis by a health professional, current treatment status, and type of medication, enabling estimation of the diagnosis-treatment-control cascade for key conditions. Behavioral risk factors assessed include tobacco use, alcohol consumption, dietary patterns, physical activity, and sexual behavior, with skip patterns and range checks built into the electronic tools to minimize data entry errors. All items are drawn from, or adapted directly from, WHO STEPS and INDEPTH Network instruments that have been widely used and validated in demographic and health surveillance sites in sub-Saharan Africa, supporting their reliability and suitability for this target population.

The household questionnaire additionally captures individual-level items on mobile phone ownership (personal or shared), primary connectivity mode (SMS, mobile data, or Wi-Fi), and internet access, providing a baseline characterization of digital access at the household and individual levels to contextualize NCD communication and service delivery in both rural and urban settings.

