### Follow-Up Procedures

Following the baseline census, longitudinal data collection rounds will be implemented annually over the 5-year surveillance period. Using the existing household and individual registers, field teams revisit each HHID and reverify the household roster, updating entries for births, deaths, in-migrations, out-migrations, and changes in marital status. Migration events are classified and dated using standard HDSS definitions, enabling calculation of person-time at risk and net migration rates. Migration events are identified and documented during each annual household roster update. New residents found in a previously mapped household who meet the standard residency criterion (at least 3 of the last 6 mo or intending to stay at least 6 mo) are classified as in-migrants, assigned a unique individual ID, and enrolled prospectively, with their origin and date of arrival recorded. Previously enrolled individuals confirmed by household members to have permanently departed the HDSS ward boundaries are classified as out-migrants, with their date of departure, destination, and reason for migration recorded and their follow-up record closed from that date, contributing person-time up to departure. Individuals who return after out-migration are reenrolled under their original ID, ensuring longitudinal continuity.

At each round, eligible adults are recontacted for updated interviews and measurements to estimate NCD prevalence and incidence, monitor changes in health-related behaviors and attitudes, and track risk factors over time. All recorded deaths are subjected to verbal autopsy using the WHO 2016 [31] standardized instrument administered on tablets; data are processed with automated cause-of-death assignment tools (eg, InterVA or InSilicoVA), given the limitations of vital registration in this setting.

Participant retention is managed through a structured recontact protocol whereby temporarily absent individuals receive at least 2 repeat visits at different times before being recorded as noncontactable for that round. At each round, the baseline characteristics of participants lost to follow-up will be compared with those retained to assess and account for potential attrition bias.

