### Data Management and Quality Assurance

A comprehensive data management framework underpins the HDSS. Data capture uses an electronic system built on REDCap with a longitudinal, relational database structure designed for population surveillance. Each household is assigned a unique HHID and each individual an INDID, enabling linkage of demographic episodes, survey data, and clinical measurements to calculate person-time at risk and event rates. Field tablets store encrypted records locally during the day; at the end of each field shift, data are synchronized via secure, password-protected connections to a central cloud-based server hosted on institutional infrastructure. Built-in validation rules (range checks, mandatory fields, and cross-variable consistency checks) run at the point of entry, with additional automated scripts on the server to detect duplicates, outliers, and missingness. Data collectors receive intensive training on the electronic tools, household listing procedures, eligibility screening, physical measurements, point-of-care devices, ethics, and field record keeping, and they are supervised by field coordinators who conduct random spot checks and reinterviews for quality control. All equipment is calibrated regularly according to manufacturer recommendations, and standard operating procedures govern every step from mapping and enrollment to follow-up and data cleaning.

To maintain secure linkage between participant identity and the assigned INDID, a separate access-restricted identity register mapping personal identifiers (full name, date of birth, and sex) to the INDID is maintained on an encrypted, password-protected server, accessible only to the principal investigator and senior data manager. All analytical datasets contain INDIDs only, with no direct personal identifiers, ensuring participant confidentiality. At each follow-up visit, fieldworkers verify the participant’s name, date of birth, and household ID verbally before accessing their longitudinal record, confirming correct identity linkage.

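### Counting out-migrants' time up to departure would bias NCD incidence low, because NCD status is ascertained only at survey rounds; in- and out-migration are also defined on different boundaries

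*Protocol article*

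**What the plan says.** The Follow-Up Procedures section of the protocol article sets the person-time rule. Out-migration is learned from others: "Previously enrolled individuals confirmed by household members to have permanently departed the HDSS ward boundaries are classified as out-migrants". The date of departure is recorded, and these people have "their follow-up record closed from that date, contributing person-time up to departure". Those who come back are re-enrolled under their original identifier.

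The next paragraph of the same section says how NCD status is obtained: "At each round, eligible adults are recontacted for updated interviews and measurements to estimate NCD prevalence and incidence". Under Data Collection Methods, self-reported NCD history also comes from the individual interview, so it too is known only at a round.

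Data Management and Quality Assurance describes household and individual identifiers "enabling linkage of demographic episodes, survey data, and clinical measurements to calculate person-time at risk and event rates". The article gives no second person-time rule for conditions found by examination.

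Entry is worded differently from exit. "New residents found in a previously mapped household who meet the standard residency criterion" are classified as in-migrants and given an individual identifier, whereas exit requires leaving the ward.

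**The concern.** Departure-date person-time is right for events the household can report whenever they happen, such as deaths, births and moves. Hypertension and diabetes are different: the study learns of onset only when it next interviews or measures the person. Someone who leaves between rounds was last assessed at the previous round. Their time from then to departure would count in the denominator, but onset in that time could not reach the numerator unless they returned and were assessed again.

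NCD incidence is one of the study's stated aims, and rural-urban contrast is another. A rate whose bias depends on mobility and round spacing could show site differences, or changes between rounds of unequal spacing, that are not real.

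The entry and exit definitions raise a second, separate problem. A person who moves from one household to another in the same ward meets the wording for in-migration at the new address but not the wording for out-migration at the old one. Net migration gains an entry with no matching exit. If the new address is not followed, nothing in the stated rules closes the record.

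**Working it through.** The article states no NCD incidence rate and no out-migration rate, so there is no figure of its own to reproduce. The out-migration rates below are assumptions.

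**Inputs**
- Round interval: 1 year (Follow-Up Procedures).
- First interval: baseline was completed in December 2024 (rural) and March 2025 (urban), and the first follow-up is planned for the second quarter of 2027 (Results). To mid-quarter this is about 2.4 years rural and 2.15 years urban; 2.25 is used as a single value.
- Out-migration hazard m: assumed 5%, 10%, 15% and 20% a year.

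**Model.** Take constant out-migration, the same onset hazard in leavers and stayers, and status ascertained at time T only in those still resident. Per person enrolled:
- stayers' time = T·e^(−mT)
- all counted time = (1 − e^(−mT))/m
- observed/true incidence ≈ stayers' time ÷ all counted time = mT·e^(−mT)/(1 − e^(−mT))

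Worked case, m = 0.10 and T = 2.25: e^(−0.225) = 0.7985. Stayers' time = 2.25 × 0.7985 = 1.797. All counted time = 0.2015/0.10 = 2.015. Ratio = 1.797/2.015 = 0.892, or 10.8% low.

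| Assumed m per year | Observed/true, T = 1 | Shortfall | Observed/true, T = 2.25 | Shortfall |
|---|---|---|---|---|
| 5% | 0.975 | 2.5% | 0.945 | 5.5% |
| 10% | 0.951 | 4.9% | 0.892 | 10.8% |
| 15% | 0.927 | 7.3% | 0.841 | 15.9% |
| 20% | 0.903 | 9.7% | 0.792 | 20.8% |

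**Check by simulation.** For 2,000,000 people with m = 10%, T = 2.25, an assumed true incidence of 3.00 per 100 person-years and onset dated at mid-interval, the stated rule gave 2.668. Dropping leavers' unassessed time gave 3.002.

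**Pooled to 2029.** With intervals of 2.25, 1 and 1 years, m = 10% and no new entrants, stayers' time is 1.797 + 0.723 + 0.654 = 3.173 and all counted time is (1 − e^(−0.425))/0.10 = 3.462. The ratio is 0.916, about 8% low.

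**Rural-urban ratio over the first interval, true rates equal** (T = 2.4 rural, 2.15 urban)

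| m rural | m urban | Rural obs./true | Urban obs./true | Apparent urban/rural ratio |
|---|---|---|---|---|
| 5% | 10% | 0.941 | 0.896 | 0.95 |
| 5% | 15% | 0.941 | 0.847 | 0.90 |
| 10% | 10% | 0.885 | 0.896 | 1.01 |
| 10% | 5% | 0.885 | 0.947 | 1.07 |

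The bias depends only on m × T, so the urban bias exceeds the rural one only if urban out-migration is more than 2.4/2.15 = 1.12 times the rural rate.

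**Migration boundary.** If a fraction w of residents a year move within the ward into a followed household, each adds one in-migration and no out-migration. Net migration is overstated by w, that is 1000·w per 1000 person-years. The article gives no value for w.

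**The case against.** The strongest reply is that the departure-date rule sits in the paragraph on migration and is not expressly named as the NCD denominator. The data-management sentence can be read as describing what the database can do. Censoring rules for examined conditions often belong in an analysis plan, which is not shown, and this is a condensed article. That much stands: the bias is conditional on the rule being applied to NCD incidence. But the point rests on a rule the article states, not on a silence. It is the only person-time rule given, and the text links demographic with clinical records to form rates.

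Some recovery is possible. Returnees can be assessed again, and deaths before departure are covered by verbal autopsy. The planned comparison of lost and retained participants addresses selection; it does not remove unassessed time from the denominator.

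A reader might infer that incidence is understated more at the urban site. The documents do not support that. The limitations section says only that loss to follow-up might be worse in mobile urban or periurban groups. The rationale describes growing rural-to-urban movement, which implies rural departures, and the first rural interval is the longer one. The direction is open.

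A reader might also take the 2.25-year figures as the general size of the bias. They apply to the first interval only; annual rounds give less than half as much.

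On boundaries, the article cites standard HDSS definitions, records origin and destination, and runs duplicate checks, so internal moves could be identified. The written definitions still do not match. The mismatch does not depend on which of the article's two descriptions of coverage (all households, or a systematic sample) applies. Under full coverage a within-ward move is still an entry with no exit; under sampling, people can also move to an unfollowed household with their record left open.

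**Conclusion.** The concern holds in conditional form. If departure-date person-time is used for NCD incidence, the rate is biased low: by about 2.5% to 10% with annual rounds and about 5% to 21% over the first interval, for out-migration of 5% to 20% a year. Those sizes rest on assumed out-migration, constant hazards, equal onset hazard in leavers and stayers, and no recovery through returnees. The downward direction needs only that leavers have some onset that is never ascertained. Distortion of the rural-urban ratio is possible, but its direction and size cannot be stated from the article.

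The boundary mismatch stands on its own: as worded, net migration is biased upward by the within-ward move rate, whose value is unknown. Both matters should be settled before the first follow-up round is analysed.

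**What to change.** - **NCD incidence.** End person-time at the last round at which the person's status was ascertained, by interview or measurement, or treat onset as interval-censored between rounds. State the assumption that leavers and stayers share the same onset hazard, or weight for out-migration. Report out-migration by site.
- **Demographic rates.** Keep departure-date person-time for deaths, births and migration.
- **Boundaries.** Use the same HDSS boundary for entry and exit. Code moves within the HDSS wards as internal moves under the original identifier and leave them out of net migration. Close or transfer the person-time of anyone who moves to a household that is not followed.

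The cost is an analysis definition and one event code, using origin and destination data already planned. NCD person-time falls slightly: in the worked case by 0.218 of 2.015 years per person (10.8%) over the first interval. That is time in which no onset could have been detected, so no detected cases are lost. Anyone who leaves before the first follow-up contributes no NCD person-time, which is why the hazard assumption or the weighting must be stated.

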### Study Aims

This paper describes the establishment of a Zimbabwe HDSS to address critical NCD surveillance gaps through 4 specific aims:

Establish a longitudinal, population-based HDSS spanning rural and urban sites to generate accurate, timely data on demographic dynamics, NCD burden, risk factors, and health care access through continuous household surveillance with regular follow-up.Characterize prevalence, incidence, and temporal trends of major NCDs—hypertension, diabetes, cardiovascular diseases, and chronic respiratory diseases—with particular emphasis on identifying undiagnosed and untreated cases through active case-finding and objective biomarker measurement.Quantify rural-urban differences in NCD burden, risk factor exposure profiles, health care–seeking behavior, treatment access, and health outcomes to inform geographically targeted interventions and evidence-based resource allocation.Generate actionable evidence informing national NCD policy development, strategic planning, resource allocation decisions, and intervention design through systematic integration with existing health systems and continuous stakeholder engagement.

By addressing fundamental gaps in existing surveillance infrastructure, this HDSS will provide the continuous, geographically granular, longitudinal data essential for evidence-based NCD prevention and control in Zimbabwe’s rapidly evolving epidemiological landscape.

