## Results

The Zimbabwe HDSS was granted ethical approval by the Medical Research Council of Zimbabwe on July 30, 2024. Community profiling and household mapping were completed in both sites in the third quarter of 2024. Baseline data collection was completed in Mt Darwin (rural site) in December 2024 and in Bindura (urban site) in March 2025. Data cleaning and quality assurance procedures for the baseline dataset were initiated in April 2025, and statistical analysis of baseline prevalence, risk factor distributions, and rural-urban comparisons is projected for completion by the first quarter of 2026, with findings expected to be submitted for publication by the end of 2026. The first annual longitudinal follow-up round is planned for the second quarter of 2027, subject to funding availability. Subsequent follow-up rounds are scheduled annually through 2029, with longitudinal incidence estimates, demographic event rates, and NCD trend analyses expected to be published progressively from 2026 onward.

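### As written, cardiovascular incidence rests on interviews with survivors, and nothing routes a cardiovascular death found by verbal autopsy into the incident cases, so the estimate would be too low

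*Protocol article*

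**What the plan says.** All references are to the protocol article.

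- **Study Aims** makes incidence an aim for several conditions: "Characterize prevalence, incidence, and temporal trends of major NCDs—hypertension, diabetes, cardiovascular diseases, and chronic respiratory diseases". The next aim is to quantify rural-urban differences in NCD burden. The Objective in the Abstract singles out cardiovascular diseases and diabetes.
- **Follow-Up Procedures** says that at each round "eligible adults are recontacted for updated interviews and measurements to estimate NCD prevalence and incidence".
- **Data Collection Methods** describes how cardiovascular disease is ascertained in the living: "Health-related modules capture self-reported history of NCDs (hypertension, diabetes, and cardiovascular disease", with questions on diagnosis by a health professional and on treatment.
- **Follow-Up Procedures** gives deaths a separate route: "All recorded deaths are subjected to verbal autopsy using the WHO 2016 [31] standardized instrument administered on tablets", followed by automated assignment of cause. Deaths are found through the household, which supplies "records of vital events (births, deaths, and in- and out-migrations) since the last round".
- **Data Management and Quality Assurance** links demographic episodes, survey data and clinical measurements by individual identifier for person-time and event rates. Verbal-autopsy cause is not in that list.
- **Data Analysis** mentions incidence rates in general terms and does not mention verbal autopsy. The Discussion describes verbal autopsy as serving cause-specific mortality.
- **Results** gives the timing. Baseline was completed in December 2024 (rural) and March 2025 (urban), and "The first annual longitudinal follow-up round is planned for the second quarter of 2027, subject to funding availability".

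**The concern.** Someone free of cardiovascular disease at baseline who has a first stroke or heart attack and dies before the next round cannot be re-interviewed. If incidence is drawn from recontacted adults, that person appears in the mortality figures and not among the incident cases. The resulting quantity is the incidence of survived events, which is lower than the incidence of first events.

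This matters most for cardiovascular disease, a named objective in which a first event can be quickly fatal. Hypertension and diabetes rarely remove a person between visits in this way, and both are measured directly by blood pressure and glucose.

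Two comparisons in the aims could also be affected. The rural-urban contrast would shift if early fatality differs between the sites. The time trend would shift because the first interval is much longer than a 12-month one, so more first events end in death before they can be reported.

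**Working it through.** The article states no cardiovascular incidence, case fatality or verbal-autopsy accuracy, so there is no figure to reproduce. The check has two parts: whether any route carries a fatal first event into incidence, and how much its absence would matter.

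**1. Routes into the incidence count**

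| Source | Can it record a first cardiovascular event? | Tied to incidence in the text? |
|---|---|---|
| Interview at recontact | Yes, if the person is alive and seen | Yes |
| Physical and biochemical measurements | No: blood pressure, heart rate, anthropometry, glucose, lipids and urine do not identify a past stroke or heart attack | Yes |
| Verbal autopsy | Yes, for fatal events | No: tied to cause of death and cause-specific mortality |
| Facility records | Possibly | No: the Discussion mentions linkage only as a potential |

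The one source that would see a fatal first event is collected, but it is not connected to incidence.

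**2. Length of the first gap**

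From baseline completion to the second quarter of 2027 (April to June):

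- rural, from December 2024: 28 to 30 months;
- urban, from March 2025: 25 to 27 months.

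**3. Size of the shortfall (assumed inputs)**

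Let m be the share of first events that are fatal before the next round. If these are not counted, observed / true incidence = 1 − m. If they are counted through verbal autopsy with sensitivity s, the ratio is 1 − m + m·s.

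| m (assumed) | Not counted | Counted, s = 0.7 | Counted, s = 0.9 |
|---|---|---|---|
| 0.20 | 0.80 | 0.94 | 0.98 |
| 0.30 | 0.70 | 0.91 | 0.97 |
| 0.40 | 0.60 | 0.88 | 0.96 |

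**4. Effect of interval length (assumed inputs)**

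Split m into early fatality f and a later death rate of 10% per year, h = −ln(0.9) = 0.105, with onset uniform over an interval of T years:

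m = 1 − (1 − f)·g(T), where g(T) = (1 − e^(−hT)) / (hT).

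g(28/12) = 0.887 and g(1) = 0.949.

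| f (assumed) | Missed over 28 months | Missed over 12 months |
|---|---|---|
| 15% | 25% | 19% |
| 30% | 38% | 34% |
| 45% | 51% | 48% |

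Going from a 28-month to a 12-month interval multiplies observed incidence by 0.949 / 0.887 = 1.07 at any f. That is an apparent rise of about 7% with no change in true incidence.

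**5. Rural-urban ratio**

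With equal true incidence, the observed ratio is (1 − m_rural) / (1 − m_urban). With the same interval and later death rate, g cancels, leaving (1 − f_rural) / (1 − f_urban):

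- equal fatality: 1.00;
- 30% rural, 20% urban: 0.70 / 0.80 = 0.88;
- 40% rural, 25% urban: 0.60 / 0.75 = 0.80.

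The three-month difference between the sites in the first gap is negligible under the same assumptions: g(29/12) / g(26/12) = 0.883 / 0.894 = 0.99.

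**The case against.** The strongest reply is that the article never says fatal events are left out. The sentence about recontact gives the purpose of one data stream and does not define an incident case. The next sentence sends every recorded death to verbal autopsy. Deaths are found through the household roster, so finding them does not depend on interviewing the person who died. Identifiers are available for linkage, and survival analyses are planned. An incident-case definition is commonly left to a full protocol or analysis plan, which is not shown.

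Much of this stands. A reader might infer that incidence is scored only in re-interviewed adults and that fatal first events are never counted. The text supports neither word: it contains no exclusion, and the silence of Data Analysis on verbal autopsy is not a restriction. What remains is that the article does more than omit a definition. It names a source for incidence, that source cannot contain fatal events, and it gives the source that can contain them a different purpose. Recording a death and its cause is not the same as counting an incident case.

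A second reply concerns the remedy. The Introduction says that many NCD cases are undiagnosed and that self-report understates prevalence. Some cardiovascular deaths in people with no reported history will therefore come from unrecognised prevalent disease, perhaps more often where diagnosis is poorer. This also stands. It is a reason to show the fatal component separately, not to leave it out of incidence.

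**Conclusion.** The point holds for cardiovascular incidence. Followed as written, the estimate would count mainly events survived to the next round and would be too low. The direction follows from the design. The size is unknown: the figures of 60% to 80% of true incidence rest on an assumed 20% to 40% of first events being fatal before the next round.

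Three stronger conclusions are not supported:

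- **All NCD incidence is affected.** The mechanism concerns acute cardiovascular events; hypertension and diabetes are not affected to the same degree.
- **The rural-urban ratio is biased.** It is distorted only if early fatality differs by site. The Introduction describes rural treatment delays and limited infrastructure, which makes a difference plausible and would make rural incidence look too low. It gives no case fatality for either site and does not say that cardiovascular fatality is higher at Mt Darwin.
- **The unequal intervals create a substantial false trend.** Under the assumptions shown it is about 7%, and it requires later intervals of 12 months.

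The rule should be stated before the first follow-up round, because cardiovascular incidence is a stated objective and the data needed are already planned.

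**What to change.** In Follow-Up Procedures and Data Analysis, define incident cardiovascular disease as the first of:

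1. a cardiovascular event newly reported at a round; or
2. a death assigned a cardiovascular cause by verbal autopsy, in a participant with no cardiovascular history at the last interview, dated at death.

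Report fatal, nonfatal and combined incidence by site.

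The cost is a few lines of text and a linkage, by individual identifier, of data the plan already collects. No extra fieldwork is needed, and the first follow-up round is still ahead in the stated schedule. The small downside is that verbal-autopsy misclassification and undiagnosed prevalent disease may put some non-incident deaths into the fatal component. Showing the components separately by site makes this visible, and the text should say so.
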